# Efficacy and safety of intramuscular administration of allogeneic adipose tissue derived and expanded mesenchymal stromal cells in diabetic patients with critical limb ischemia with no possibility of revascularization: study protocol for a randomized controlled double-blind phase II clinical trial (The NOMA Trial)

**DOI:** 10.1186/s13063-021-05430-2

**Published:** 2021-09-06

**Keywords:** Phase II clinical trial, Randomized, Adipose-derived mesenchymal stromal cells, Critical limb ischemia, Diabetes mellitus, Cell therapy, Advanced therapy medicinal products

## Abstract

**Background:**

Chronic lower limb ischemia develops earlier and more frequently in patients with type 2 diabetes mellitus. Diabetes remains the main cause of lower-extremity non-traumatic amputations. Current medical treatment, based on antiplatelet therapy and statins, has demonstrated deficient improvement of the disease. In recent years, research has shown that it is possible to improve tissue perfusion through therapeutic angiogenesis. Both in animal models and humans, it has been shown that cell therapy can induce therapeutic angiogenesis, making mesenchymal stromal cell-based therapy one of the most promising therapeutic alternatives. The aim of this study is to evaluate the feasibility, safety, and efficacy of cell therapy based on mesenchymal stromal cells derived from adipose tissue intramuscular administration to patients with type 2 diabetes mellitus with critical limb ischemia and without possibility of revascularization.

**Methods:**

A multicenter, randomized double-blind, placebo-controlled trial has been designed. Ninety eligible patients will be randomly assigned at a ratio 1:1:1 to one of the following: control group (*n* = 30), low-cell dose treatment group (*n* = 30), and high-cell dose treatment group (*n* = 30). Treatment will be administered in a single-dose way and patients will be followed for 12 months. Primary outcome (safety) will be evaluated by measuring the rate of adverse events within the study period. Secondary outcomes (efficacy) will be measured by assessing clinical, analytical, and imaging-test parameters. Tertiary outcome (quality of life) will be evaluated with SF-12 and VascuQol-6 scales.

**Discussion:**

Chronic lower limb ischemia has limited therapeutic options and constitutes a public health problem in both developed and underdeveloped countries. Given that the current treatment is not established in daily clinical practice, it is essential to provide evidence-based data that allow taking a step forward in its clinical development. Also, the multidisciplinary coordination exercise needed to develop this clinical trial protocol will undoubtfully be useful to conduct academic clinical trials in the field of cell therapy in the near future.

**Trial registration:**

ClinicalTrials.govNCT04466007. Registered on January 07, 2020. All items from the World Health Organization Trial Registration Data Set are included within the body of the protocol.

## Background

Critical lower limb ischemia (CLI) is characterized by chronic pain at rest, ulcers or gangrene attributable to a proven occlusive arterial disease [1]. The evolution of CLI, in the context of a generalized atherosclerotic disease, implies high morbidity and mortality. CLI develops earlier and with greater intensity in patients with diabetes mellitus, with complications that may result in the amputation of the limb and even death [2, 3]. A public health goal of the standard of care is to decrease global cardiovascular risk through the control of risk factors by changes on lifestyle habits (quitting smoking, healthy diet, physical exercise) and pharmacological treatment (antiplatelet therapy, statins) [4]. However, there is insufficient evidence to show that this approach improves substantially the course of this disease [5]. Surgical or endovascular revascularization is often the treatment of choice, despite the fact that it is an invasive procedure that carries a high rate of complications. In addition, the health cost of this pathology is quite high. The treatment of the diabetic foot, and specifically critical limb ischemia, is the second most expensive complication in economic terms for the health system, just behind dialysis [6]. Efforts to prevent loss of the affected limb also include soft tissue debridement, minor amputations, and even skin grafts, all of which are costly procedures. In this context, given the high number of amputations that are still practiced annually worldwide, we are still in need of a cost-effective and easy-to-apply treatment [7]. Recently, research has shown that it is possible to improve tissue perfusion through therapeutic angiogenesis, making it one of the most promising strategies used to promote the proliferation of collateral vessels in ischemic tissues. In this sense, there are several methods to improve tissue perfusion, such as the administration of recombinant growth factors [8–11], or the constitutive expression of genes that encode for these factors through gene therapy [12]. Although both therapies have shown to promote angiogenesis in ischemic conditions in preclinical models [13], modest results were obtained when clinically applied [14–17]. In contrast, it has been shown both in animal models and in humans that cell therapy can induce therapeutic angiogenesis [18–20]. Cell-based therapies aiming to promote vascular regeneration gained interest with the discovery of a subpopulation of vasculogenic endothelial progenitor cells as reported by Asahara et al [17]. Human endothelial cell progenitors were isolated from peripheral blood by magnetic bead selection based on cell surface antigen expression. In animal models of ischemia, these cells have the ability to colonize the site of injury of ischemic tissue and secrete a number of vascular growth factors that can lead to clinically effective neovascularization [17]. It seems that these cells contribute to angiogenesis through the secretion of angiogenic cytokines and proteases such as matrix metalloproteases (MMPs), among others, helping the stability and growth of the endothelial and vascular network [21]. In 2002, the pioneering results of the TACT study (Therapeutic Angiogenesis using Cell Transplantation study) were published, consisting of a pilot uncontrolled safety study (*n* = 25) and a randomized controlled clinical trial to evaluate the use of mononuclear cells of bone marrow (BM) by intramuscular injection in 22 patients for treat peripheral arterial disease (PAD). Cell therapy with BM-derived mononuclear cells significantly improved ABI (difference 0.09 [95% CI 0.06–0.11]), transcutaneous oxygen pressure (pTcO2), (13 [9–17]), rest pain (− 0.85 [− 1.6 to − 0.12]) and pain-free walking time (1.2 [0.7–1.7]) in all treated patients [22]. Unfortunately, those with poorly controlled diabetes were excluded from the trial. As the prevalence of PAD increases in patients with type 2 diabetes mellitus (type 2 DM) it is logical to assume that this population group is a potential candidate for cell therapy [22]. Since then, several studies have been carried out in which the transplantation of the mononuclear fraction of BM or peripheral blood has been shown to improve the endothelial function in the territories in which they were administered [23] and to improve ischemic pain and the healing of ulcers [24]. In a phase I/II, open-label, non-comparative clinical trial, safety and feasibility of treatment with autologous mesenchymal stromal cells (MSC) derived from BM and administered intra-arterially in patients with type 2 DM and lower limb ischemia was studied. All of the participants (*n* = 20) showed an increase in leg vascularization demonstrated by angiography and 100% of the ulcers healed. During the first year of follow-up, 7 minor amputations were performed, but no patient suffered a major amputation [25]. Cañizo et al. reported the first case of a patient with CLI treated with peripheral blood CD133+ cells. There were no major amputations and after 17 months of follow-up, patients experienced symptomatic and functional improvement. The group also observed the appearance of blood flow in the posterior tibial artery that was absent before the procedure [26]. The search for the most appropriate cell type for this pathology remains a challenge today [27], but the use of MSC is gaining prominence. The fact that these cells have trophic, immunomodulatory, and anti-inflammatory properties and liposuction is an easy and minimally invasive technique places them as suitable candidates for clinical use. The study that we propose here focuses on the development and optimization of an advanced therapy medicinal product (ATMP) based on adipose tissue-derived MSC (Ad-MSC) to be administered intramuscularly to patients with type 2 DM and CLI within a multicenter randomized phase II clinical trial, favoring the translation of this cellular therapy to clinical practice. If proven safe and effective, an accessible, easy and minimally invasive treatment will be available for patients without any other option or that can even be associated with existing surgical treatments and improve their results.

The objectives of this study are the following:
To evaluate the safety and tolerability of the intramuscular administration of allogeneic Ad-MSC in patients with type 2 DM with critical lower limb ischemia and no possibility of revascularizationTo evaluate the preliminary efficacy of the treatmentTo evaluate the quality of life of participants of the study after treatment administration

## Methods

### Study design

This is a study protocol of a multicenter, randomized, placebo-controlled, double-blinded, dose-finding, phase II clinical trial of three parallel groups to evaluate safety and efficacy of the intramuscular administration of allogeneic Ad-MSC in diabetic patients with CLI and without possibility of revascularization, over conventional treatment. The overall study design is reported according to the CONSORT statement and agrees with the SPIRIT 2013 checklist.

A total of 90 eligible patients will be recruited from ten academic hospitals in Spain (Jimenez Diaz Foundation University Hospital, La Paz University Hospital, Navarra University Clinic, Gregorio Marañón General University Hospital, Virgen de la Arrixaca University Clinical Hospital, Salamanca University Hospital, Victoria Eugenia-Cruz Roja Española Hospital, La Fe Clinical and Polytechnic University Hospital, Valladolid Clinical University Hospital and Alicante General University Hospital). Participants will be randomly assigned into control group, low-cell dose treatment group, or high-cell dose treatment group, at a ratio 1:1:1.The flowchart of the trial is presented in Fig. 1 and the study procedures schedule is shown in Table 1. Recruitment period will last 1.5 years, and follow-up period will be 1 year. The expected total duration of the study, from the first visit of the first patient to the last visit of the last patient, will be 2.5 years.

**Fig. 1 Fig1:**
[figure not shown]
Flowchart: 90 patients will be recruited in the study and randomly allocated to three groups (high-dose group = 30; low-dose group = 30; control group = 30). The assessment will be done 24 h and 3, 6, and 12 months, respectively

**Table 1 Tab1:** Schedule of study procedures

	Study period						
	Enrolment		Treatment	Follow-up			
Timepoint	***V-1, selection visit***	***V0, baseline visit***	V1, treatment	***V2, 24 h***	***V3, 3 m***	***V4, 6 m***	***V5, 12 m***
	***Day − 30 to day − 21***	***Day − 20 to − 1***	Day 0	***Day 1***	***Day + 90 ± 7***	***Day + 180 ± 15***	***Day + 365 ± 15***
***Eligibility criteria***	X	X					
***Informed consent***	X						
***Anamnesis***	X						
***Physical examination***	X		X	X	X	X	X
***Blood test***	X				X	X	X
***Urine pregnancy test***	X						
***Rutherford-Becker category***	X						
***Ankle-arm index***	X				X	X	X
***Ulcers evaluation (Wifi classification)***	X				X	X	X
***VAS scale***	X			X	X	X	X
***Gastrocnemius muscle perimeter***	X				X	X	X
***Temperature of the limb***	X				X	X	X
***Neuropathic symptoms***	X				X	X	X
***Quality of life scales (SF-12 and VascuQol-6)***	X				X	X	X
***MRI***	X						X
***Randomization***		X					
***Pre surgical evaluation***		X					
***Treatment administration***			X				
***Concomitant medication***	X	X	X		X	X	X
***Adverse events***			X	X	X	X	X

*MRI* magnetic resonance imaging, *h* hours, *m* month, *v* visit

### Recruitment of eligible participants

Patients will be recruited by the attending clinicians (vascular surgeons) among the population of chronic, type 2 DM patients with peripheral arteriopathy that is usually under periodic follow-up in the outpatient clinic. Proposal to participate in the clinical trial will take place in one of these routine outpatient visits. Clinicians will explain to each subject the nature of the study, its purposes, procedures, expected duration, and the potential risks and benefits related to participation in the trial, as well as any inconvenience that this may entail. Patients will have enough time to read and understand the explanations before dating and signing the informed consent and will receive a copy of the signed document. Eligible patients will be (1) those aged between 40 and 90 years; (2) with type 2 DM diagnosed for more than one year; (3) with severe vascular arteriosclerosis, defined as Rutherford-Becker (RB) category 4 and 5 [23], mono or bilateral; and (4) with impossibility of surgical or endovascular revascularization or failure of revascularization surgery performed, at least 30 days before inclusion in the study. Patients with CLI and tissue loss in the target limb (RB category 6) or previous major amputation in the target limb will be excluded from the trial. Detailed eligibility criteria are described in ClinicalTrials.gov (NCT04466007). During trial conduct, periodic contacts with investigators and a trial newsletter are foreseen to assess possible difficulties in recruitment in advance and to keep investigator team informed of recruitment evolution. No specific methods to minimize attrition are foreseen. Eligible patients are severely ill patients that are usually adherent to medical visits, and thus a high drop-out rate is not expected.

### Blinding, randomization and allocation concealment

Masking of participants will be guaranteed as follows: the solution for intramuscular infusion of Ad-MSC (active treatment) will have the same aspect as HypoThermosolFRS (placebo), and the syringes will be identified by a label that will exclusively contain the information corresponding to the clinical trial and the patient code. However, since the density of each product may be different, it is assumed that there is a risk that the clinical investigator administering the treatment may know which treatment is being applied. For that reason and to ensure double blind, each center will count, as a minimum, with two investigators per enrolled patient: a non-blinded investigator who will administrate cellular therapy and a blinded investigator who will perform the assessment of participants as described in Table 1. Randomization will be performed through the electronic case report form (eCRF). Study subjects will be assigned to group 1, 2, or 3, at a ratio 1:1:1, based in a random block sequence prepared by the sponsor’s statistical service. The assigned group information from each participant will not be visible in the eCRF. Then, an email with the assigned treatment group information of the participant will be sent automatically to non-blinded team. No stratification process has been designed in the randomization scheme. If a phase III clinical trial is subsequently developed, stratification will be defined, according to preidentified factors that could influence efficacy outcomes. During the study, masking can be broken in the event of a serious adverse event (SAE) related to the study medication that requires urgent medical treatment. The researcher will notify the sponsor within a maximum period of 24 h and sign the SAE notification form that will be sent by fax or email to the person in charge of pharmacovigilance of the study. The sponsor will communicate to the investigators any information that may affect the safety of the trial subjects as soon as possible. In the event of unmasking, blinding will be maintained for those responsible for evaluating the primary variable and for those responsible for data analysis and interpretation of the results.

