#### Secondary outcome measures

Efficacy will be assessed through the following variables:

(a) Vascularity in the target limb will be assessed through mean change in percentage of vascular flow measured by MRI in the target limb at 12 months from baseline between groups. MRI will be centrally read by a blinded radiologist. (b) Disease severity will be evaluated through percentage of patients with an improvement in RB category at 3, 6, and 12 months from baseline [33] between groups. This scale is usually used in patients with chronic arterial disease to classify chronic arterial disease into clinical categories (category 0, asymptomatic; category 1, mild claudication; category 2, moderate claudication; category 3, severe claudication; category 4, pain at rest; category 5, minor tissue loss; category 6, ulcer o gangrene). (c) Ulcer healing (if any) will be assessed through the percentage of patients with a decrease in SVS-“WIfI” wound classification [34, 35] at 3, 6, and 12 months from baseline between groups. SVS-WIfI classification aims to be as functional in diagnosing PAD as the tumor-node-metastasis-based diagnosis system (TNM). Three measurable parameters are collected: wound (extension and depth), ischemia (blood flow), and foot infection (presence and extension). (d) PAD evolution will be evaluated by % of patients with an increase in ankle-brachial index at 3, 6, and 12 months from baseline between groups [36]. (e) Pain intensity will be assessed through mean change in visual analogue scale (VAS) from 0 to 10 cm, as described by the patient (0, absence of pain; 1–3, mild; 4–7, moderate; 8–10, severe) and percentage of patients with an improvement in pain intensity at rest at 3, 6, and 12 months from baseline between groups. (f) Percentage of patients with a decrease in temperature (°C), increase in gastrocnemius muscle perimeter (cm) and decrease in neuropathic symptoms of the treated limb compared with contralateral at 3, 6, and 12 months from baseline. (g) Mean change in percentage of amputations in each group at the end of the study will be registered.

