### Statistical considerations

#### Sample size calculation

A formal size calculation based on the expected differences for the primary outcome has not been performed. This is a phase II, dose-finding study, and no previous data on the preliminary efficacy of Ad-MSC with CLI including type 2 DM patients are available to date. A sample size of 30 patients per group was deemed appropriated based on the possibility to reach normality and the feasibility to recruit 90 eligible patients in 10 university hospitals.

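### Binary efficacy outcomes are compared without adjustment for baseline Rutherford-Becker category (4 versus 5), which is known before an unstratified randomisation into arms of 30; a stratified test would protect against chance imbalance at almost no cost

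*Protocol article*

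**What the plan says.** All references are to the protocol article.

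- **Randomisation** (Blinding, randomization and allocation concealment). Patients are allocated "at a ratio 1:1:1, based in a random block sequence prepared by the" sponsor's statistical service. The section adds "No stratification process has been designed in the randomization scheme". For a possible later phase III trial, "stratification will be defined, according to preidentified factors that could influence efficacy outcomes".
- **Population** (Recruitment of eligible participants). Severe disease is "defined as Rutherford-Becker (RB) category 4 and 5". The Secondary outcome measures section describes category 4 as pain at rest and category 5 as minor tissue loss.
- **Timing** (Table 1). RB category is recorded at the selection visit (V-1), and randomisation takes place at the baseline visit (V0).
- **Outcomes** (Secondary outcome measures). "Disease severity will be evaluated through percentage of patients with an improvement in RB category at 3, 6, and 12 months from baseline". Wounds are handled separately: "Ulcer healing (if any) will be assessed through the percentage of patients with a decrease in" the wound classification.
- **Analysis** (Statistical analysis). Qualitative outcomes are compared by chi-square, or alternatively Fisher's exact test. There is a global three-group comparison and four further contrasts: each dose versus placebo, high versus low dose, and both doses versus placebo. P values are Bonferroni-corrected. No covariate is named.
- **Size** (Sample size calculation). "A sample size of 30 patients per group was deemed appropriated". "A formal size calculation based on the expected differences for the primary outcome has not been performed".

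**The concern.** The protocol admits two severity groups that are known before allocation, and several efficacy outcomes plausibly depend on the starting category: RB improvement, relief of rest pain and amputation. It accepts that some factors could influence efficacy, but leaves their use to a later and presumably larger trial. Chance imbalance matters more in arms of 30.

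Two things are at stake for the secondary efficacy comparisons:

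- If two arms happen to differ in RB mix, part of their observed difference reflects severity rather than treatment, and the unadjusted test cannot separate the two.
- If RB predicts response, ignoring it wastes power that a trial of this size can hardly spare.

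The tests are fixed in the protocol and the baseline value is already collected, so this is a choice that can be improved and not a detail left out.

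**Working it through.** The protocol gives no power, response rate or imbalance probability, so there is no figure of its own to reproduce.

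**Inputs from the protocol:** three arms of 30; no stratification; two RB categories at entry; unadjusted tests; four contrasts with Bonferroni correction.

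**Assumptions, because the protocol is silent:** the share *p* of RB 5 patients, the response rates by category, and the treatment effect.

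**Step 1. Chance of imbalance.** A 20-point gap in arms of 30 is 0.20 × 30 = 6 patients. Take the RB 5 counts X1, X2, X3 as independent Binomial(30, *p*) and enumerate exactly:

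- one named pair: P(|X1 − X2| ≥ 6)
- any of the three pairs: P(max − min ≥ 6)

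| RB 5 share | One named pair | Any of three pairs |
|---|---|---|
| 10% | 1.8% | 4.6% |
| 20% or 80% | 7.5% | 17.4% |
| 30% or 70% | 12.0% | 26.6% |
| 40% or 60% | 14.7% | 31.4% |
| 50% | 15.5% | 33.0% |

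Holding the total number of RB 5 patients fixed changes little (any pair: 17.2%, 26.3%, 31.1% and 32.6% for the last four rows). For both doses pooled (60) versus placebo (30), the chance of a 20-point gap is 3.2% at a 20% share and 8.6% at 50%.

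**Step 2. What such a gap does.** Suppose response without effective treatment is 50% in RB 4 and 10% in RB 5. A 20-point gap in RB mix then produces a spurious expected difference of 0.20 × (50 − 10) = 8 points. With 40% and 20% it is 0.20 × (40 − 20) = 4 points.

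**Step 3. Type I error, two arms of 30, half RB 5, no treatment effect (simulation).** At 50%/10% the unadjusted chi-square rejects in about 5% of all trials, but in about 11% of trials where that pair differs by 20 points or more. CMH stratified by RB stays near 5% in those same trials. A second set of assumed rates points the same way: at 20% in RB 4 and 60% in RB 5, chi-square rejects in 4.9% overall and 9.8% given such a gap.

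**Step 4. Power, two arms of 30, half RB 5, two-sided 5% (simulation).** The common log odds ratio is 1.4, so the odds ratio is exp(1.4) ≈ 4.06. At 50%/10% the treated odds are 1.00 × 4.06 = 4.06 in RB 4 (80%) and 0.111 × 4.06 = 0.451 in RB 5 (31%).

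| Assumed placebo response, RB 4 / RB 5 | Chi-square | CMH by RB |
|---|---|---|
| 50% / 10% | 52–53% | 62% |
| 40% / 20% | 71% | 72% |
| 35% / 25% | 74.9% | 74.3% |

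If Bonferroni over the four contrasts is taken as 0.05 / 4 = 0.0125, the first row becomes about 32% versus 40% and the second 50.6% versus 50.8%. Where RB barely matters, CMH loses about one point at 5% and up to about two points at 0.0125.

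**Step 5. What stratified randomisation would add.** With permuted blocks within RB category, the RB 5 counts of two arms could differ by at most 1, 2 or 3 patients for blocks of 3, 6 or 9 (block size is not stated). A 20-point gap could then not occur. Power, however, hardly changes once the analysis is adjusted: CMH has 62.4% with unstratified and 63.3% with balanced strata at 50%/10%, and 72.1% versus 72.6% at 40%/20%.

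**The case against.** The strongest case against is that nothing here is an error. Block randomisation without strata is valid. The choice is disclosed, the trial is a phase II dose-finding study whose efficacy aim is preliminary, and overall type I error is preserved. The power gain of about ten points depends on response rates found nowhere in the protocol and nearly vanishes at milder ones. Most efficacy outcomes are changes from the patient's own baseline, which removes some of the influence of starting severity. Further adjusted analyses may sit in an analysis plan that is not shown.

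Much of this stands. It rules out several stronger readings that a reader might infer:

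- **That about three trials in ten would have a misleading comparison.** That figure is for the worst of three pairs at an RB 5 share of 30–70%. For one named contrast it is 12–16%, and the split is unknown.
- **That RB is the main prognostic factor.** The protocol uses it to measure disease severity but ranks no factors.
- **That the trial's primary conclusion is at risk.** The primary outcome is treatment-related complications, and nothing in the protocol ties these to RB category.
- **That each arm's RB 5 count is its number evaluable for ulcer healing.** The protocol's scale lists category 5 as minor tissue loss and places ulcers or gangrene in category 6, so the two cannot simply be equated.
- **That the randomisation must be changed.** Step 5 shows that nearly all the power gain comes from the analysis.

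What the objection does not remove is that the primary tests of the efficacy outcomes are fixed as unadjusted, while a baseline severity measure is already in hand. Validity averaged over all possible randomisations does not help in the one trial that turns out imbalanced.

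**Conclusion.** The point holds as an improvement to the analysis of the binary secondary efficacy outcomes. It is not a flaw in the randomisation or a threat to the primary safety comparison.

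The imbalance figures depend only on the assumed RB split: 26–33% for any pair and 12–16% for one pair at 30–70% RB 5, falling to 17% and 7.5% at 20/80. The consequences depend on how prognostic RB is. At an assumed 50% versus 10% they are material: about 11% conditional type I error, and roughly ten points of power lost. At 40% versus 20% the power gain is about one point. The case for change rests on this asymmetry, since the possible benefit is useful and the worst cost found is one to two points of power.

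The power and type I error calculations cover two-arm comparisons of a binary outcome. They say nothing about the pain and quality-of-life scores analysed by analysis of variance or Kruskal-Wallis.

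**What to change.** In the Statistical analysis section, name CMH stratified by baseline RB category (4 versus 5, as recorded at the selection visit) as the test for binary secondary efficacy outcomes that apply to both categories. Use an exact stratified test where counts are small, in place of Fisher. Keep the global comparison, the listed contrasts and the Bonferroni correction. Fix the wording before unblinding. Wound healing, assessed only in patients with a wound, stays outside this change.

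**Cost:** analysis wording only. No new data are needed. The named downside is a power loss of about one point if RB is barely prognostic, or up to about two points at an alpha of 0.0125.

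**Optional, only if enrolment has not started:** use RB category as the single stratum of the block randomisation, without centre strata. This needs a second block list in the eCRF and may leave one incomplete block per stratum, so arm sizes could differ by a patient or two. It prevents visible RB imbalance but adds about one point of power or less once the analysis is adjusted. If enrolment has started, keep the existing list and change only the analysis.
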